### Criteria for success

This feasibility trial will be deemed successful and lead to the development of a proposal for an adequately powered randomised controlled trial if:1. At least one of the exercise programmes is shown to be acceptable, based on a combination of data from participant interviews, the number and type of adverse events in each group and exercise session adherence rates (at least 67% of participants completing at least 24 of the 36 sessions).2. At least 24 patients are recruited during the 12-month recruitment window (based on recruitment from three NHS Hospital Trusts and 1–2 recruits per site per two months).3. At least 67% of participants provide valid cardiorespiratory fitness, disease activity (CDAI) and quality of life (IBDQ) data at the 13-week follow-up visit.

The criteria for success will provide the basis for interpreting the results of this study and determine whether it is appropriate to proceed to a full trial and if any modifications need to occur for a full trial to be feasible.

### Ethical and safety considerations

The research study will follow the Health Research Authority’s processes for gaining NHS permissions and approvals. We are confident that the assessment procedures and exercise programmes will be safe. Exercise testing has been demonstrated to be safe for patients with CD [30] and other chronic diseases [31, 32]. Nevertheless, patients’ suitability for the study will be assessed by a clinical co-investigator, and participants will be closely monitored during all training and testing sessions. Furthermore, exercise sessions will be supervised by experienced staff who are trained in resuscitation. Exercise training will be discontinued if a clinical co-investigator deems it necessary (e.g. if a patient experiences a disease relapse) or if the participant withdraws consent. The trial will also be subject to oversight from an independent Trial Steering Committee.

### Safety reporting

Adverse event reporting will be conducted in accordance with the Sponsor’s Adverse Event Reporting Procedures. A clinical co-investigator will be responsible for determining the causality and seriousness of adverse events and ensuring that appropriate action is taken. Information about adverse events will be collected from the beginning of any study-related procedure (i.e. when written consent has been obtained). The adverse event reporting period will stop at the participant’s final trial contact, i.e. at the 26-week follow-up.

We will record all serious adverse events, as well as all non-serious adverse events that are either deemed to be related to participation in the research or result in withdrawal from an exercise programme or the study. Serious adverse events are defined as any untoward medical occurrence that falls in one of the following criteria: results in death; is life threatening; requires unplanned or prolonged hospitalisation; results in persistent or significant disability or incapacity; or results in a congenital abnormality or birth defect. Non-serious events are defined as untoward medical occurrences that do not fulfil any of the serious adverse event criteria.

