### Outcome measures

#### Feasibility and acceptability outcomes

The main focus of this study is feasibility and acceptability of procedures for recruitment, allocation, measurement, retention and the intervention procedures. Recruitment rates will be measured as rate of invited participants who are eligible and consenting and will be reported in a Consolidated Standards of Reporting Trials (CONSORT) participant flowchart. Acceptability of allocation procedures will be assessed by examining reasons for dropout in discontinuing participants and comparing attrition rates between the three study groups and between participants who did and did not receive their preferred allocation (assessed prior to randomisation). Suitability of measurement procedures will be evaluated based on completion rates and rates of missing data. Attrition rates will be established as discontinuation of intervention and loss to follow-up measurement for all groups. The acceptability of the exercise programmes will be assessed using session adherence rates, measures of exercise enjoyment (see the Interventions section) and participant and provider feedback via telephone interviews conducted after the 26-week follow-up visit. The participant interviews will last up to 30 min and will cover perceived benefits and negative consequences from participating in the study, feedback regarding specific design features of the study (including the exercise protocol and assessment procedures) and perceptions of barriers and facilitators to intervention participation. The safety of exercise training will also be assessed by exploring rates of disease relapse at 13 weeks, reasons for dropout from the exercise programmes and the number and type of adverse events, both CD specific and general, which occur in each group.

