### Blinding

Blinding of trial participants and the intervention facilitator is not possible. Questionnaires will be completed by the participants independently and checked by a researcher for completeness. Anthropometric, cardiorespiratory fitness and disease activity outcomes will be assessed by researchers blinded to group allocation. Participants will be asked not to disclose their allocation to the technician.

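### The recording rule for non-serious adverse events drops unrelated events in every arm and ascertains the rest unequally, so it cannot supply the by-group counts that the safety outcome and success criterion 1 use

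*Protocol article*

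**What the plan says.** Three sections of the protocol article bear on this.

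- **Feasibility and acceptability outcomes.** Safety is to be explored through relapse rates at 13 weeks, reasons for dropping out of the exercise programmes, and "the number and type of adverse events, both CD specific and general, which occur in each group".
- **Criteria for success.** Criterion 1 asks whether at least one exercise programme is acceptable, judged from interviews, "the number and type of adverse events in each group" and session adherence. Only adherence has a numerical threshold.
- **Safety reporting.** Serious events are covered without restriction: "We will record all serious adverse events". Beyond these, the record is limited to "non-serious adverse events that are either deemed to be related to participation in the research or result in withdrawal from an exercise programme"; read to its end, the condition is that such events are "deemed to be related to participation in the research or result in withdrawal from an exercise programme or the study". On who decides: "A clinical co-investigator will be responsible for determining the causality and seriousness of adverse events". Collection starts at consent, and "The adverse event reporting period will stop at the participant’s final trial contact, i.e. at the 26-week follow-up".

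The Background section states the first objective as exploring acceptability, safety and potential benefit relative to usual care. The Blinding section says "Blinding of trial participants and the intervention facilitator is not possible". It lists anthropometric, fitness and disease activity outcomes as assessed blind; causality of adverse events is not on that list.

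**The concern.** The outcome and the success criterion need counts of events by group. The recording rule decides which events exist in the data, and it depends on two things that differ between arms: whether an event can be attributed to the research, and whether the participant leaves something because of it.

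The error could run either way. Ordinary symptoms noticed at frequent sessions and judged related could look like harm from exercise. Conversely, a real excess of symptoms could disappear if the events are judged unrelated and nobody withdraws. The counts alone could not tell these cases apart. Because this is a rule about data collection, an analysis plan cannot repair it: an event that was never written down cannot be recovered. The counts feed the decision on whether to proceed to a full trial.

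**Working it through.** **1. Which events enter the record.** Applying the Safety reporting rule to each arm:

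| Event | Exercise arms | Usual care |
|---|---|---|
| Serious | recorded | recorded |
| Non-serious, judged related to the research | recorded (sessions and assessments) | recorded (assessments only) |
| Non-serious, leads to leaving the study | recorded | recorded |
| Non-serious, leads to leaving only the exercise programme | recorded | route does not exist |
| Non-serious, judged unrelated, no withdrawal | not recorded | not recorded |

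The last row conflicts with the promise to report general as well as Crohn's-specific events in each group. The fourth row is an asymmetry in the rule itself. The Ethical and safety considerations section makes it concrete, since it gives disease relapse as an example of a reason to discontinue training. On a natural reading, a non-serious relapse that ends training is recorded whatever its cause. The same relapse in a control who stays in the study is recorded only if judged related to the research.

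**2. Opportunity to notice events.** Exercise participants have 3 sessions × 12 weeks = up to 36 supervised sessions, each with a case report form (Interventions; Data management). For usual care, the text schedules assessments at baseline, week 13 and week 26, and nothing between baseline and week 13. Figure 1 is not available to check this.

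**3. What CDAI relapse covers.** It is measured in all participants before randomisation and at week 13, and is assessed blind. Relapse means a rise of at least 100 points to a level above 150. It does not pass through the relatedness rule. It misses a flare that resolves before week 13, a flare that begins after week 13 (although event collection runs to week 26), and any worsening of less than 100 points.

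**4. Size, by illustration.** The plan's own sample size reproduces: 12 / (1 − 0.20) = 15 per arm, and 3 × 15 = 45. The documents give neither an event rate nor the share of events that would be recorded, so both are assumptions here.

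Expected recorded events = n × p × f, where n = 15, p is non-serious events per person and f is the share recorded. With p = 0.5 in every arm, 15 × 0.5 = 7.5 events occur per arm.

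- Usual care, f = 0.05 to 0.10: 7.5 × 0.05 = 0.38; 7.5 × 0.10 = 0.75.
- Exercise arm, f = 0.20 to 0.50: 7.5 × 0.20 = 1.5; 7.5 × 0.50 = 3.75.

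If p is read instead as the chance that a participant has one such event, the chance that usual care records none is (1 − p × f)^15. This is 0.975^15 = 0.68 at f = 0.05 and 0.95^15 = 0.46 at f = 0.10.

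Varying p from 0.3 to 0.7:

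| p | Usual care, f = 0.05–0.10 | Exercise arm, f = 0.20–0.50 |
|---|---|---|
| 0.3 | 0.23–0.45 | 0.9–2.25 |
| 0.5 | 0.38–0.75 | 1.5–3.75 |
| 0.7 | 0.53–1.05 | 2.1–5.25 |

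The opposite error also follows. Suppose the true rates are 0.7 with exercise and 0.3 without, and f is 0.05 to 0.10 in both arms. The true excess of 15 × (0.7 − 0.3) = 6 events then shrinks to 0.3 to 0.6 recorded events.

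**The case against.** A reader might infer that the usual-care record is empty by design and that the safety part of criterion 1 therefore cannot be answered. The documents do not support this. Serious events are recorded in every arm. Withdrawal from the study counts, and controls can withdraw. Relatedness is to taking part in the research rather than to exercise, and controls undergo a fitness test to exhaustion and blood sampling at baseline and week 13. An illustration that set recording in usual care at zero would assume its own conclusion.

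Three further objections have weight.

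- Blinded CDAI relapse is an unfiltered safety measure in all arms, so a relapse present at week 13 cannot be lost through a causality call. This stands, within the limits in step 3 of the working. Criterion 1, however, names adverse events and does not name relapse.
- Criterion 1 sets no threshold or test for adverse events, and the Statistical analysis section rules out hypothesis testing. Serious events, related events and withdrawals within the exercise arms bear directly on acceptability. This stands, and it confines the problem to the comparison of non-serious events between groups.
- The sponsor's adverse event procedures and the case report forms are not shown, so how events are elicited at visits cannot be judged. This also stands. It does not remove the conflict between the recording rule and the promised outcome, both of which the article states.

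**Conclusion.** The point holds for non-serious events. As written, the rule cannot deliver the Crohn's-specific and general events by group that the outcomes section promises and criterion 1 draws on. Unrelated events without withdrawal are missing in every arm. Those that are recorded are ascertained differently by arm and are likely to be sparse in usual care.

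The asymmetry of routes and contacts follows from the text, subject to Figure 1. Its numerical effect does not: 0.38–0.75 against 1.5–3.75 recorded events rests on an assumed equal rate of 0.5 per person and assumed recording shares of 5–10% and 20–50%. If the shares were equal, there would be no spurious gap, only low counts. The comparisons of serious events and of CDAI relapse are not affected.

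**What to change.** Reconcile the Feasibility and acceptability outcomes, Criteria for success and Safety reporting sections in one of two ways.

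- **Option A: widen the record.** Record Crohn's-specific non-serious events in all three arms regardless of relatedness, using the same short set of questions at the existing week 13 and week 26 contacts. Tabulate events detected during supervised sessions separately, for the exercise arms only, and do not set them against usual care.
- **Option B: narrow the claim.** State that the by-group safety comparison covers serious events and CDAI-defined relapse, and describe other events within the exercise arms only.

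Option A costs one extra case report form page and a modest increase in recorded events, with no new visits. Its weakness is self-report by unblinded participants, so blinded CDAI relapse should stay alongside it. Option B costs only a change of text, but gives up any by-group statement on milder, transient or later Crohn's events.

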### Data management

Paper case report forms will be used to collect study outcome data. An exercise session case report form will also be completed for each exercise session for participants in the two exercise intervention groups. Examples of the case report forms will be stored in the Trial Master File. Each centre’s personnel will receive training from members of the Trial Management Group in the study requirements, including how to complete the case report forms, how to conduct the assessments (e.g. cardiopulmonary exercise tests, blood sampling) and how to deliver the interventions. The study case report forms will be stored in participant files, which in turn will be stored in numerical order in a secure, restricted access location. The Chief Investigator (LB) and Trial Manager (GT) will regularly review case report forms to ensure that they are being completed appropriately, and they will conduct a site monitoring visit once a site has recruited three participants.

Data on paper case report forms will be manually entered into customised spreadsheets in Microsoft Excel. Entered data will be double-checked by a second researcher. Once completed, these spreadsheets will be password encrypted and then transferred electronically to the statistician at York Trials Unit using the University of York’s secure document DropOff Service. Data validation plans will be implemented by the statistician to identify data points that do not fall within an expected range of values. Following data cleaning, the data will be summarised and analysed according to the statistical analysis plan.

Essential trial documentation (i.e. the documents which individually and collectively permit evaluation of the conduct of a clinical trial and the quality of the data produced) will be kept with the Trial Master File and Investigator Site Files. The Sponsor will ensure that this documentation will be retained for a minimum of 5 years after the conclusion of the trial to comply with standards of Good Clinical Practice. Case report forms will be stored for a minimum of 5 years after the conclusion of the trial as paper records and a minimum of 20 years in electronic format. All paper records will be stored in a secure storage facility or off-site by the University of Hertfordshire. All electronic records will be stored on a password-protected server.

### Dissemination

The dissemination strategy for this research will be to inform a wide range of local, national and international audiences about the results and conclusions. It must, however, be remembered as part of this strategy that the current project is preliminary work aimed at informing a subsequent definitive clinical trial.

Health professionals—we aim to publish our research in journals that cover the relevant medical specialties and with preference for those that deposit publications in open access databases to increase free dissemination. In addition, we aim to present this research at appropriate national and international conferences.

Users—from this perspective, we aim in the first instance to collaborate with our patient representatives and local experts in the patient and public involvement to best facilitate user dissemination. We plan to write a specific news piece that will be forwarded to appropriate groups and organisations.

Service managers—as an exploratory study, it is unlikely that results from this study will directly influence commissioning processes in the short term. Moreover, we will engage with appropriate primary and secondary care groups to discuss support for our proposed definitive study leading on from this research.

## Discussion

Regular physical exercise may benefit several aspects of physical and mental health in people with inflammatory bowel disease; however, the evidence base is sparse. The EXACT study is a rigorously designed randomised controlled feasibility trial that will provide useful preliminary information about the acceptability and effectiveness of two common modes of supervised exercise training (high-intensity interval training and moderate-intensity continuous training) in people with inactive or mildly active Crohn’s disease. The findings will inform the development of a future adequately powered, multi-centre, randomised controlled trial.

### Trial status

Recruitment started in April 2016 and is ongoing.

## Abbreviations

CD: Crohn’s disease
CDAI: Crohn’s Disease Activity Index
CRF: Case report form
EXACT: Exercise for Adults with Crohn’s disease Trial
FS: Feeling Scale
HADS: Hospital Anxiety and Depression Scale
HIIT: High-intensity interval training
IBD: Inflammatory bowel disease
IBDQ: Inflammatory Bowel Disease Questionnaire
IPAQ: International Physical Activity Questionnaire
MICT: Moderate-intensity continuous training
NHS: National Health Service
PACES: Physical Activity Enjoyment Scale
RPE: Rating of perceived exertion
*W*peak: Peak power output
